**RESEARCH PARTICIPANTS**

The research participants will be health professionals from primary care and tuberculosis reference centers. The criteria for participating in the research correspond to: over 18 years of age and having at least six months of service for health professionals. Exclusion criteria: declaring not wanting to be a participant in the research, being an intern or having less than six months of effective service.

**DATA COLLECTION INSTRUMENT**

For data collection, a semi-structured interview will be used (APPENDIX B). When relating discursive practices with the production of meaning, it is assumed that the meanings are not in language as materiality, but in the discourse that makes language the tool to build reality (SPINK, 2004). The interview materializes, through language, this individual's experience, which is, for Shotter, a psychological instrument or tool through which we establish different relationships with those around us and produce meaning for our circumstances, enabling the communication of this meaning (apud PINHEIRO , 2004).

The interview will consist of two parts: one for the identification of the interviewees and another for the guiding questions. The formulation of the questions will be natural, it is often not interesting to ask a direct question, but to lead the respondent to remember part of his life. For that, the researcher can very well provoke his memory (BOURDIEU, 2002).

The guiding questions will be separated for the two focus groups and described below:

For Primary Care professionals:

- What do you know about latent tuberculosis infection (LTBI)?

- How do you perform the treatment of LTBI?

- Did you have prior knowledge of Isoniazid 300mg?

- Did you feel safe using Isoniazid 300mg?*

- Was the information material available on Isoniazid 300mg sufficient?

- How was the distribution/dispensing flow of Isoniazid 300mg in your workplace?

- Have you noticed any difference in patients using Isoniazid?

300mg?

For Tuberculosis Reference Center Professionals:

- Did you have prior knowledge of Isoniazid 300mg?

- Did you feel safe using Isoniazid 300mg?*

- Was the information material available on Isoniazid 300mg sufficient?

- How was the distribution/dispensing flow of Isoniazid 300mg in your workplace?

- Have you noticed any difference in patients using Isoniazid?

300mg?

*The term usage tries to encompass the entire process (from prescription to dispensing) by all professional categories involved (doctor, nurse, pharmacist, technicians).

The interview, essentially describing the identification of the research participant, will be carried out individually. The data to be collected by the researchers will strictly follow those induced by the guiding questions available in a script. In the interview, the technique of free association will be used which, according to Tura (1997), has been shown to be especially useful in studies of stereotypes, perceptions and attitudes, elements that make up the structure of social representations. Therefore, in the community, respondents will be asked at the beginning what the word tuberculosis reminds them of or suggests.

Lefèvre and Lefèvre (2005a) emphasize that the fact that it is a qualitative research does not allow the interviewer to introduce new questions, however, if there is a need to facilitate the continuity of the testimony during the interview, add phrases such as: " What else?" "Have you anything else to say?" "Like this?" "Because?" "Want to supplement with something else?"

Before starting each interview, the subjects will be informed about the objectives of the study and the importance of the recording, assuring them of the confidentiality of all statements and the freedom to refuse to participate in the research or to suspend it at any time, without prejudice to him who was asked to sign a Free and Informed Consent Term (APPENDIX A).

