Thus, the triad for the correct use of a medication composed of: prescription, dispensing and ingestion needs to be monitored and questions related to the professionals who carry out the prescription, to those who participate in the dispensing process, which differs in each service, and also, questions related to drug intake by the patient bring together a new configuration in Tuberculosis programs and will therefore be the object of this study, as described in Figure 1.
[figure not shown]

Figure 1 - Processes related to the triad of evaluation of new dosage

Thus, with the development of the present study, it is intended to understand the process of implementation of the presentation of Isoniazid 300mg for the treatment of LTBI in some health units in different regions of the country in order to identify potential risks in the process of using the drug. medication and ensure patient safety.

To carry out this study, three steps will be adopted that may occur simultaneously. The first stage will be a pragmatic clinical trial with patients LTBI diagnosed in health facilities in Brasília, Curitiba, Florianópolis, Ribeirão Preto - SP and Vitória, which will evaluate the prescription, dispensing and ingestion of the two dosages provided by the PNCT. The second stage will be a cross-sectional study using the 'Knowledge, attitude and practices' methodology to verify compliance in prescribing and dispensing. And the third stage will be a qualitative study with health professionals to analyze the speeches of professionals who prescribe the drug and professionals who dispense the new dosage of 300mg. In this sense, the evaluation of this new presentation will consist of stages that complement each other, as shown in Figure 2:

[figure not shown]

Figure 2. Steps for the Evaluation of Implementation of Isoniazid 300mg for the treatment of LTBI

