# OBJECTIVE

• To analyze the occurrence of serious or unexpected adverse reactions resulting from the use of Isoniazid 300mg by the patient for the treatment of latent tuberculosis infection.

• To analyze the patient's use of Isoniazid 300mg for the treatment of latent tuberculosis infection.

• To analyze the information strategies made available to health services on the new presentation of Isoniazid 300mg for the treatment of latent tuberculosis infection.

• To analyze compliance in the prescription of Isoniazid 300mg for the treatment of latent tuberculosis infection through the Knowledge, Attitudes and Practices (CAP) strategy.

•To analyze compliance in the dispensing of Isoniazid 300mg for the treatment of latent tuberculosis infection through the Knowledge, Attitudes and Practices (CAP) strategy.

• To determine the plasma levels of patients undergoing treatment with Isoniazid 100 and 300mg

• To analyze the social representations of health professionals from the basic unit on the use of Isoniazid 300mg for the treatment of latent tuberculosis infection.

• To know the meanings of health professionals at the basic unit about the use of Isoniazid 300mg for the treatment of latent tuberculosis infection.

• To identify the role of health professionals from the basic unit in relation to patients using Isoniazid 300mg for the treatment of latent tuberculosis infection.

• To interpret how health professionals at the basic unit relate their conceptions to the prescription of Isoniazid 300mg for the treatment of latent tuberculosis infection.

• To develop and analyze the use of a computerized system for mobile devices that helps health professionals in the diagnosis and treatment process, as well as to assist in the prevention and care of people with latent Tuberculosis, evaluating its use in these health services to integrate follow-up actions as well as evaluating the degree of solvability of these actions from the system.

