The Collective Subjects' Discourses are the gathering of the E-CH present in the testimonies, which have CIs with a similar or complementary meaning, to give them the form of chained sentences. It is important to point out that the CI is not an interpretation, but a description of the meaning of a statement or a set of statements. The technique for building the DSC involves selecting, from each individual answer to a question, the E-CHs, which are the most significant parts of these answers. These E-CH correspond to ICs, which are the synthesis of the discursive content manifested in the E-CH. With the material of the E-CHs of similar CIs, synthesis discourses, or CSDs, are constructed in the first person singular, with a collectivity appearing as if it were an individual discourse. (LEFÈVRE; LEFÈVRE, 2005b).

The CSD represents the thinking of a collectivity, through a series of testimonies that culminate in synthesis discourses, which bring together responses from different individuals, with discursive content of similar meaning, which begins to express or represent social speech or collective thinking. in the first person singular (LEFÈVRE; LEFÈVRE, 2005b).

According to Lefèvre and Lefèvre (2005b), the “I” of the CSD is an attempt to rescue the “social or collective self”; more precisely, it is a resource created to bring out the social unconscious that speaks in the individual. Therefore, the CSD is a discourse to signal what society imposes on the individual through the unconscious internalization of their discourses, which is why it needs to be stated in the first person singular. The speeches reveal what the community thinks, how it thinks, and how this thought is distributed in the social space (LEFÈVRE; LEFÈVRE and MARQUES, 2009).

Subjects will be identified with the capital "C" consonant, followed by the Arabic number increasing from 1. Example: C1; C2; C3; C4. Duarte, MAMEDE & ANDRADE (2002) propose that the complete transcripts of the recorded testimonies be attached to the research, so that they can contribute to the reliability and legitimacy of the results. Even so, it was decided not to put this material in an appendix, as it was considered that reading the individual speeches in full could compromise the confidentiality commitment assumed with the interviewees.

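### Stage 3: the stated free-association word is tuberculosis, not the use of Isoniazid 300mg, and the protocol contradicts itself on whether content is collected individually or in focus groups

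*Protocol*

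**What the plan says.** **Object.** The Protocol's OBJECTIVE section includes this aim: "To analyze the social representations of health professionals from the basic unit on the use of Isoniazid 300mg". Neighbouring aims ask for the meanings and conceptions that professionals attach to the same use. The INTRODUCTION says the third stage is "to analyze the speeches of professionals who prescribe the drug and professionals who dispense the new dosage of 300mg".

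**Respondents.** RESEARCH PARTICIPANTS: "The research participants will be health professionals from primary care and tuberculosis reference centers".

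**Association step.** DATA COLLECTION INSTRUMENT justifies free association as useful for studying perceptions and attitudes, described as "elements that make up the structure of social representations". It then sets the prompt: "Therefore, in the community, respondents will be asked at the beginning what the word tuberculosis reminds them of or suggests".

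**Collection mode.** The same section says: "The guiding questions will be separated for the two focus groups and described below". It also describes one interview in two parts, identification and guiding questions, and adds: "The interview, essentially describing the identification of the research participant, will be carried out individually". In the second stage, the data-collection section calls the later qualitative work a focus group study held in Brasília.

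**Analysis.** DATA ANALYSIS describes how the collective subject discourse (abbreviated both CSD and DSC) is built: "The technique for building the DSC involves selecting, from each individual answer to a question, the E-CHs". E-CHs are key expressions.

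**The concern.** There are two separate problems of fit between objective, instrument and analysis.

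The first is the stimulus. Associations to the word *tuberculosis* describe how professionals see tuberculosis in general. The stage asks how they see the use of a particular isoniazid presentation for latent infection, a state that the INTRODUCTION distinguishes from active disease. The location phrase suggests lay respondents, whom this stage does not recruit.

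The second is the collection mode. A site reading the protocol cannot tell whether to put the guiding questions to one person at a time or to a group. The choice matters because the analysis presents thinking as shared on the strength of separate individual answers. In a group, agreement may partly reflect what earlier speakers said. A promise to keep all statements confidential is also beyond the investigators' control once colleagues have heard each other.

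**Working it through.** The stage has no stated sample size, power or number of sessions, so there is no figure to reproduce. The check sets the texts side by side and makes one count.

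**1. Object against stimulus**

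| Element | What the protocol gives | Section |
|---|---|---|
| Object of the representation | Use of Isoniazid 300mg for latent infection | OBJECTIVE |
| Respondents | Health professionals in primary care and reference centres | RESEARCH PARTICIPANTS |
| Reason for free association | It reaches components of social representations | DATA COLLECTION INSTRUMENT |
| Stimulus word | *tuberculosis* | DATA COLLECTION INSTRUMENT |
| Where it is asked | In the community | DATA COLLECTION INSTRUMENT |

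The sentence fixing the stimulus follows directly from the justification and opens with a word of consequence. On the text, the prompt is therefore more than a courtesy opener, and neither its word nor its setting matches the object or the respondents.

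**2. How far the mismatch reaches**

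Count of guiding questions in DATA COLLECTION INSTRUMENT:

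- Primary care: 7, of which 5 name Isoniazid 300mg and 2 concern latent infection.
- Reference centres: 5, all naming Isoniazid 300mg.
- Total: 7 + 5 = 12. Of these, 5 + 5 = 10 name Isoniazid 300mg and 2 concern latent infection, so 12 of 12 are on the topic.

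The interview therefore does gather material on the stated object, and the mismatch is limited to the association step. Two features keep it from being trivial. Of the five Isoniazid 300mg questions common to both lists, four can be answered yes or no (prior knowledge, feeling safe, sufficiency of material, noticing a difference) and the fifth asks about distribution flow. None asks openly what the presentation means to the respondent. The section also bars the interviewer from adding questions and allows only neutral prompts, so an association about tuberculosis in general cannot be steered towards the drug.

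**3. Collection mode**

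| Text | Points to |
|---|---|
| Second stage, data collection: the qualitative work is a focus group study | Group |
| Guiding questions separated for two focus groups | Group |
| What is done individually is essentially identification | Content questions in a group, by implication |
| One interview in two parts, the second being the guiding questions | Individual, since the interview is individual |
| Information and consent before each interview; interviews transcribed | Individual |
| Third Stage method and DATA ANALYSIS: discourse built from individual speech and each individual answer | Individual |

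The two sets of statements cannot both describe the procedure for the guiding questions. The analysis clearly needs the individual mode.

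**4. Consequence if groups were held**

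Speaker-labelled transcripts would recover part of what the analysis needs. However, the protocol does not say that every member answers every question, and answers given after hearing others are not separate. DATA ANALYSIS withholds full transcripts to protect confidentiality, yet group members would hear those same statements directly.

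**The case against.** The strongest defence is that the tool for this objective is the semi-structured interview with its guiding questions, and the association prompt is only one opening item. The protocol says that collection follows the guiding questions, and DATA ANALYSIS describes no separate analysis of association data. Starting broadly also agrees with the protocol's remark that direct questions are often unhelpful. Much of this stands. A reader might infer that the objective is left unanswered. The documents do not support that, since all 12 guiding questions are on topic. What the defence does not explain is why a technique adopted to reach social representations is given a word other than the thing represented.

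A reader might also infer that no other association item exists. That cannot be checked: the interview instrument is placed in Appendix B, which is not in the available text. The point covers only the one stimulus stated in the protocol. Nor does any text show that the opening word distorts later answers.

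The location phrase may be loose wording, because the protocol elsewhere uses *community* for the collective whose thinking is studied. Even so, it misleads where it stands.

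On the second half, *two focus groups* introduces two professional categories and could simply mean two groups of respondents. That reading is fair, and it is why the defect is a contradiction and not an established plan to hold group sessions. It does not account for the second stage's reference to a focus group study.

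**Conclusion.** The point holds in two limited parts.

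- The one free-association stimulus stated in the protocol text does not match the stage's object, and its stated setting does not match its respondents. The effect is confined to the association step.
- The protocol contradicts itself on whether content is collected individually or in focus groups, while the stated analysis relies on individual answers.

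The harms from dependence between speakers and loss of confidentiality are conditional: they arise only if group sessions are held. It would be tempting to say that the guiding questions then rest on just two independent sources. The documents do not support that, because they give neither the number of sessions nor the number of participants, and the method is a qualitative synthesis without sampling inference.

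Severity is minor. No numerical size can be given, and the randomized comparison of the two presentations is unaffected. The conclusion assumes that Appendix B does not already correct the stimulus.

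**What to change.** 1. In DATA COLLECTION INSTRUMENT, make *isoniazid 300mg* or *treatment of latent tuberculosis infection* the association stimulus, or add one of these alongside the present word. Delete the reference to the community. Carry the same change into the Appendix B script if needed. The cost is a few words.
2. Reconcile the second stage's data-collection section with the third stage's DATA COLLECTION INSTRUMENT so that one collection mode is stated throughout. Individual interviews within the two professional groups (primary care and reference centres) fit the stated analysis and the confidentiality promise without altering either. The cost is protocol wording and, if group sessions had been intended, somewhat more interview time.

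### The qualitative stage has an objective on professionals' role with patients using isoniazid 300mg, but no listed guiding question targets it, so the data on it would be indirect (minor)

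*Protocol*

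**What the plan says.** The OBJECTIVE section of the Protocol lists, among the aims that by content belong to the qualitative stage, "To identify the role of health professionals from the basic unit in relation to patients using Isoniazid 300mg". Next to it stands a separate aim, "To interpret how health professionals at the basic unit relate their conceptions to the prescription of Isoniazid 300mg", so role is meant as something distinct from conceptions about prescribing.

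Under Third Stage, DATA COLLECTION INSTRUMENT, the guiding questions are printed in two lists. Five questions about 300mg are common to both, and primary care staff get two more on LTBI in general. A footnote explains that use, in the question on feeling safe, is meant to cover the process from prescription through dispensing for every professional category.

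The same section ties the interview to that script. The data "will strictly follow those induced by the guiding questions available in a script", and "the fact that it is a qualitative research does not allow the interviewer to introduce new questions". The latter sentence continues with an exception: where the testimony needs help to keep going, the interviewer may use short neutral prompts that ask for a reason or for anything further.

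**The concern.** An objective needs a source of data. Here the questions are fixed in advance, the interviewer may not add to them, and none asks basic-unit staff what they do with or for patients using 300mg. Information on role would then appear only if a respondent happened to mention it while answering something else.

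What is at stake is whether the qualitative stage can report on this one aim with more than incidental remarks. A sparse result could be misread as professionals seeing little role for themselves, when they had simply not been asked.

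**Working it through.** No sample-size or error-rate calculation applies. The check sets the listed questions against the objective, and then asks whether anything else in the plan could supply the missing topic.

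**1. The guiding questions, from DATA COLLECTION INSTRUMENT**

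| Question | Asked of | Form | Targets role with 300mg patients? |
|---|---|---|---|
| What the respondent knows about LTBI | Primary care | Open | No: knowledge |
| How the respondent carries out LTBI treatment | Primary care | Open | Nearest: own practice, but 300mg is not named |
| "Did you have prior knowledge of Isoniazid 300mg" | Both | Yes/no | No: awareness |
| "Did you feel safe using Isoniazid 300mg" | Both | Yes/no | No: confidence; the footnote widens it from prescription to dispensing |
| "Was the information material available on Isoniazid 300mg sufficient" | Both | Yes/no | No: information supply |
| How 300mg was distributed and dispensed at the workplace | Both | Open | No: logistics, though some role content may surface |
| Whether any difference was noticed in patients on 300mg | Both | Yes/no | No: concerns the patient, not the professional |

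Primary care list: 2 + 5 = 7 questions, 3 open and 4 yes/no. Reference-centre list: 5 questions, 1 open and 4 yes/no. Questions targeted at role with patients using 300mg: 0 of 7 and 0 of 5.

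**2. What the interviewer may add.** New questions are barred. The permitted prompts extend an answer on the topic just raised, so they can deepen a reply about safety or dispensing. They cannot bring in role with 300mg patients if nothing has led there. The opening free association uses the word tuberculosis, not the 300mg tablet.

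**3. How far the footnote reaches.** It stops at dispensing. The INTRODUCTION describes a triad of prescription, dispensing and ingestion, and the Phase 1 text of the First Step has the responsible professional guide participants on taking the medicine and on possible adverse effects. That contact with the patient around intake lies beyond the footnote's span, and no listed 300mg question covers it.

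**4. What the analysis can recover.** The Third Stage DATA ANALYSIS section builds the collective discourse from key expressions chosen within each person's answer to a question. It treats central ideas as descriptions of meaning and not as interpretations. Content that respondents do not state is therefore not available to be inferred later.

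**The case against.** The case against the point has real force in four places.

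- **Role content is elicited indirectly.** Primary care staff, the closest match to the basic unit in the objective, are asked openly how they carry out LTBI treatment, in an interview about the introduction of 300mg. The dispensing-flow question is also open, and the footnote ties the safety question to what each category of professional does. This stands, and it is why the data are called indirect and not absent.
- **An objective need not have its own question.** The method reads testimonies exhaustively and separates out themes. That is true, but a theme must first be voiced, and the fixed script leaves that to chance for this topic.
- **Other material may help.** The Second Stage gathers practices from those who prescribe, dispense and monitor. The practice groupings described there concern whether treatment is indicated and where the presentations are stored, which is not role with patients on 300mg. The questionnaire itself is not shown, so some contribution cannot be excluded.
- **Appendix B is not shown.** The section nevertheless presents its lists as the guiding questions, so the point rests on what the Protocol states.

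A reader might go further, because four of the five 300mg questions are yes/no and the section remarks that "it is often not interesting to ask a direct question, but to lead the respondent to remember part of his life". From this one could infer that the guide breaks the Protocol's own rule and that all four questions must be reworded. The documents do not support that. The remark says what is often so and sets no rule, and the section also says that questions will be phrased naturally. A yes/no question followed by a permitted request for the reason works much like an open one. The count of four describes grammar, not the data obtained, and rewording them is a matter of preference.

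**Conclusion.** The mismatch is real and small. One stated objective has no guiding question aimed at it in either list, and the bar on new questions means the interviewer cannot supply one in the session. Evidence on the role of basic-unit professionals with patients using 300mg would be indirect and would depend on what respondents volunteer.

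Two assumptions underlie this: that the printed lists are the guiding questions actually used, and that the primary care list is the one meant to serve the basic-unit objective. The Protocol does not assign objectives to stages, so placing this aim in the qualitative stage is a reading of its content.

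It would be too strong to say that the objective is left without any data. The point has no bearing on the randomised trial's primary outcome, sample size, analysis or error rates.

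**What to change.** Add one open question to the primary care list in DATA COLLECTION INSTRUMENT, asking what the professional does with and for patients using isoniazid 300mg over the course of treatment. The other questions can stay as they are. The cost is a slightly longer interview and somewhat more text to transcribe and code; the design and the method of analysis do not change.

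The SCHEDULE places the qualitative fieldwork in September 2018. If the interviews are already complete, no question can be added. The report should then state that this objective was addressed only indirectly and name the questions from which the material on role was drawn.
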